### Sample size and statistical considerations

The goal of this ongoing trial is to show non-inferiority of the PCT guided antibiotic management approach in comparison to enforced guidelines for the primary endpoint (i.e. the disease-specific failure rate within 30 days). To estimate the frequency of the primary endpoint, we used the data from our previous intervention trials [11,12,14]. Based on these data, the risk of disease-specific failure in evaluable patients is assumed to be around 15% and, if losses to follow-up are treated as failures, the failure rate of all patients may increase to 20%. We assume non-inferiority if the disease specific failure for patients on procalcitonin-guided antibiotic therapy is less than 7.5% higher compared to those on guidelines-enforced management. Based on these estimates and assumptions, a minimal number of 1002 patients (501 patients per arm) are required. Table 2 displays the power calculations for different assumed failure differences and non-inferiority boundaries with a one-sided type I error of 5% and a power of 80% to 90%. With 1002 patients, we have 80% power to exclude differences in failure rates of more than 9–12% in the respective LRTI subgroups and of ≥6% in death rates. In practice, a fixed recruitment period of 18 months is considered and all patients recruited in that period be randomized unless sample size after 18 months is below 1002 patients, which would lead to an extension of the recruitment period. The target size at each centre is 250 patients completed per protocol.

**Table 2 T2:** Required total sample size

True assumed failure rate in both arms	Required total sample size		
	Δ = 5% Power 90% (80%)	Δ = 7.5% Power 90% (80%)	Δ = 10% Power 90% (80%)

10%	1278 (932)	578 (426)	330 (244)
15%	1792 (1302)	806 (588)	458 (334)
20%	2232 (1624)	**1002 **(730)	570 (418)

Sample size calculation for the primary endpoint, i.e. required sample size to conclude at the one-sided 5%-level that the disease-specific failure rate in PCT-guided arm is at most Δ higher compared to management with enforced guidelines with a power of 80–90%.

The primary analysis population is the full analysis set which includes all randomized patients following an intention-to-treat principle. For the primary analysis, losses to follow-up (on both arms) are regarded as treatment failures. A (two-sided) 90% confidence interval for the difference of the disease-specific failure rates will be calculated based on Cochran's test stratified by type of LRTI. If the confidence interval for the difference excludes 7.5% or more, the primary objective will be met. As a sensitivity analysis, the primary analysis will be repeated on the subset of patients with evaluable outcome only, i.e. drop-outs are excluded from this additional analysis, as well as the per-protocol population which excludes non-evaluable cases and major protocol violators.

In a second step, the primary endpoint will be explored for association with potential prognostic factors in a logistic regression. The factors that will be considered are: age, sex, LRTI subgroup, PSI and CURB65 score in CAP patients and GOLD criteria and Anthonisen type of exacerbation in COPD patients [18,23]. Potential centre effects will be tested by including centre and physician as a random effect.

The trial data and sample base will be used for several pre-specified additional analyses. Theses projects include the development of clinical prediction rules for adverse medical outcomes in community-acquired LRTIs and to compare the diagnostic and prognostic accuracy of promising new biomarkers (e.g. proadrenomedullin (proADM), pro atrial natriuretic peptide (MR-proANP), copeptin, total and free cortisol) with traditional clinical signs and symptoms, the PSI and the CURB-65 score for patients with CAP and the Anthonisen criteria for patients with AECOPD [3,6,18,24-29].

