This protocol describes a randomized open multicenter intervention trial with an expected high external validity. However, contamination within the proposed open trial design is obvious. We expect that in a setting where physicians know that they are monitored for antibiotic use, the antibiotic prescription will be lower as compared to the real-life setting (Hawthorne effect). Similarly, adherence to the current guidelines in the guideline group may be higher as compared to the real-life setting. On the other hand, physicians may learn from their experience with PCT testing and change their clinical practice for the treatment of the guideline patients and for example may reduce antibiotic treatment or treatment duration in guideline group patients (spill-over effect). The latter bias, however, will be conservative. Thus, experience gained from treating patients according to the PCT algorithm in the intervention arm or other factors attributable to the conduct of the study (for example increased awareness by physicians because of more conscious decision making) may affect antibiotic prescription in the guideline arm and could lead to reduced prescribing or treatment duration in the control group.

It cannot formally be excluded that these biases could favour similarity of the two arms and thus be non-conservative for the primary non-inferiority comparison. However, for all secondary endpoints where superiority of the PCT group is the objective, we believe these biases to be conservative.

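### Counting losses to follow-up as failures in both arms dilutes the difference that the 7.5-point margin is meant to judge; with equal, outcome-independent loss at the planned level the one-sided error is about 6.9%, not 5%.

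*Protocol article*

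**What the plan says.** All references are to the protocol article, mostly to Sample size and statistical considerations.

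- **Margin.** Non-inferiority is assumed if disease-specific failure on procalcitonin guidance "is less than 7.5% higher compared to those on guidelines-enforced management". The failure events listed under Outcomes and adverse events are recurrence, complications, ICU admission, disease-related readmission and death. Loss to follow-up is not among them.
- **Handling of losses.** "For the primary analysis, losses to follow-up (on both arms) are regarded as treatment failures". The objective is met if the two-sided 90% confidence interval from this analysis excludes 7.5 points or more.
- **Planning rates.** "the risk of disease-specific failure in evaluable patients is assumed to be around 15" per cent, and "if losses to follow-up are treated as failures, the failure rate of all patients may increase to 20" per cent. The trial is sized at the higher rate: "a minimal number of 1002 patients (501 patients per arm) are required".
- **Error and power.** Table 2 is calculated "with a one-sided type I error of 5% and a power of 80% to 90" per cent.
- **Other analyses.** The evaluable-only and per-protocol analyses are sensitivity analyses. The text attaches no consequence to a result that disagrees with the primary one.

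**The concern.** Counting every loss as a failure is usually called a worst-case rule. For a superiority claim it is cautious, because it pulls the arms together. For a non-inferiority claim the same pull works in favour of the claim. Each arm receives a block of failures that has nothing to do with treatment, the real difference is measured only in the patients who were followed up, and the margin stays at 7.5 points.

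This is the trial's main safety conclusion: that withholding or shortening antibiotics on procalcitonin does not raise failure by 7.5 points or more. If the deciding analysis is diluted, the stated 5% chance of wrongly accepting such an excess is not what the plan delivers. The result also becomes sensitive to how many patients each arm loses, which says little about the treatment.

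**Working it through.** **Inputs from the article:** one-sided alpha 5%; margin 0.075; failure 15% in evaluable patients and 20% with losses counted as failures; 501 per arm; no true difference assumed for power (Table 2 column "True assumed failure rate in both arms").

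**Assumptions for this check:** unpooled normal approximation, unstratified (the plan's interval is stratified by type of infection); lost patients would fail at the same rate as evaluable ones; equal loss L in both arms, except in step 5.

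**1. The plan's own figure.** Per arm, n = 2 × 0.20 × 0.80 × (1.645 + 1.282)² / 0.075² = 487.2, so 488 per arm and 976 in total. Adding a continuity term of 1/0.075 = 13.3 per arm gives 500.5, so 501 per arm and 1002 in total. The planned size is reproduced.

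**2. Implied loss.** 0.15(1 − L) + L = 0.20, so L = 0.05/0.85 = 5.88%.

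**3. Error at the margin.** Take a true 15% v 22.5%.

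- Guideline arm: 0.0588 + 0.9412 × 0.15 = 0.2000.
- PCT arm: 0.0588 + 0.9412 × 0.225 = 0.2706.
- Difference as analysed: 0.075 × 0.9412 = 0.0706.
- SE = √(0.2000 × 0.8000/501 + 0.2706 × 0.7294/501) = 0.0267.
- P(declare non-inferiority) = Φ((0.075 − 0.0706)/0.0267 − 1.645) = Φ(−1.48) = 6.9%.

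A simulation of 1,000,000 trials gave 7.0%. The evaluable-only analysis of the same trials gave 5.0%.

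**4. Other levels of equal loss.** The article gives no loss rate beyond the one implied in step 2, so the other rows are assumptions.

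| Loss in each arm | Difference seen (true 7.5) | One-sided error | Power, losses as failures | Power, evaluable only |
|---|---|---|---|---|
| 3% | 7.28 | 6.0% | 93.0% | 94.8% |
| 5% | 7.12 | 6.6% | 91.4% | 94.5% |
| 5.9% (implied) | 7.06 | 6.9% | 90.7% | 94.3% |
| 10% | 6.75 | 8.4% | 87.6% | 93.4% |

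Power is at no true difference with 1002 randomised.

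**5. Unequal loss (assumed), true excess still 7.5 points.**

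- Guideline 6.9%, PCT 4.9%: 20.9% v 26.3%, seen as 5.4 points, error about 19%.
- Guideline 4.9%, PCT 6.9%: 19.2% v 27.9%, seen as 8.7 points, error about 1.8%.
- Guideline 5.88%, PCT 6.45%: the two effects cancel and the error is 5.0%.

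**6. Power.** Under the rule, the rate is 20% with 501 per arm: Φ(0.075/0.02527 − 1.645) = 90.7%. Evaluable only, the rate is 15% with 501 × 0.9412 = 471.5 per arm: Φ(0.075/0.02325 − 1.645) = 94.3%. The two curves cross at a true difference of about 4 points. Below that the imputed analysis succeeds less often; above it, more often, which is the inflation of step 3.

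**The case against.** **The effect is small and its input is soft.** At the implied loss the difference moves by 7.50 − 7.06 = 0.44 points and the error by about 2 points. The 15% and 20% are round planning values; 16% in evaluable patients would imply 0.04/0.84 = 4.8% loss. The interviewer must contact the GP or hospital when a patient cannot give adequate information or has been rehospitalised, which should limit loss. All of this stands, and it keeps the point modest.

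**The direction is not fixed.** A reader might infer that the error always exceeds 5%, or might quote the 19% alone. The article supports neither. It gives no reason to expect more loss in one arm, the day-30 interviewers are blinded, and the mirror case is 1.8%. About 0.6 points more loss in the PCT arm restores 5%.

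**The trial is not underpowered.** A reader might infer a power defect. There is none: the sample size was set at 20%, and 501 per arm gives 90.7%. The 94.3% is a gain available from another analysis, not a shortfall in the plan.

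**The article has not conceded the point.** Potential limitations says that certain biases "could favour similarity of the two arms and thus be non-conservative for the primary non-inferiority comparison", but this refers to monitoring and spill-over effects on prescribing. It shows that the authors recognise the principle, not that they applied it to missing outcomes.

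**The evaluable-only repeat is already planned.** The dilution would therefore be visible, but nothing follows if the two analyses disagree. That gap remains.

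**Conclusion.** The point holds as a modest, conditional inflation. With similar, outcome-independent loss at the level the plan itself implies, the deciding analysis has a one-sided error of about 6.9% instead of 5%. Across assumed equal losses of 3% to 10% the range is 6.0% to 8.4%. Without equal loss, the error can move well above or well below 5%, and the decision rule has no guard against that.

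The conclusion rests on the margin applying to disease-specific failure, as the article states. If the endpoint were failure or loss combined, the error would be 5%, but the article does not define it so. The conclusion also assumes that lost patients fail like evaluable ones. The planned 90% power is not in question.

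**What to change.** 1. Make the deciding analysis all randomised patients, with missing 30-day outcomes multiply imputed from baseline and in-hospital data already collected (type of infection, centre, age, severity, reassessments up to discharge). Alternatively, keep the present analysis and require the planned evaluable-only analysis to exclude 7.5 points as well.
2. Under the first option, keep losses-as-failures as a sensitivity analysis.
3. Add the unfavourable case: PCT losses as failures, guideline losses as non-failures.
4. Report loss to follow-up by arm, and report the per-protocol result alongside. It need not become a mandatory second hurdle: the article gives no rate of major protocol violations, so the power cost of that condition cannot be calculated.

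**Cost.** Some wording, a little programming, and reliance on a missing-at-random assumption, which item 3 tests. No extra patients are needed for the first option: Table 2 requires 806 at 15%, and 806/0.9412 = 857 randomised, below 1002. The evaluable-only calculation (94.3%) is a guide to its power; multiple imputation itself was not simulated. Under the second option both analyses must succeed, so at no true difference power is at most 90.7% and at least 90.7 + 94.3 − 100 = 85.0%. The first option is therefore preferable.

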**Methods and design::**

We describe a prospective randomized controlled non-inferiority trial with an open intervention. We aim to randomize over a fixed recruitment period of 18 months a minimal number of 1002 patients from 6 hospitals in Switzerland. Patients must be >18 years of age with a lower respiratory tract infections <28 days of duration. Patients with no informed consent, not fluent in German, a previous hospital stay within 14 days, severe immunosuppression or chronic infection, intravenous drug use or a terminal condition are excluded. Randomization to either guidelines-enforced management or procalcitonin-guided antibiotic therapy is stratified by centre and type of lower respiratory tract infections. During hospitalization, all patients are reassessed at days 3, 5, 7 and at the day of discharge. After 30 and 180 days, structured phone interviews by blinded medical students are conducted. Depending on the randomization allocation, initiation and discontinuation of antibiotics is encouraged or discouraged based on evidence-based guidelines or procalcitonin cut off ranges, respectively. The primary endpoint is the risk of combined disease-specific failure after 30 days. Secondary outcomes are antibiotic exposure, side effects from antibiotics, rate and duration of hospitalization, time to clinical stability, disease activity scores and cost effectiveness. The study hypothesis is that procalcitonin-guidance is non-inferior (i.e., at worst a 7.5% higher combined failure rate) to the management with enforced guidelines, but is associated with a reduced total antibiotic use and length of hospital stay.

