### Intervention

Clinicians in the emergency departments of participating clinics are advised to access a web based study algorithm and enter baseline data of all eligible patients with LRTI on admission and to check all inclusion and exclusion criteria prior to randomisation (figure 1). Randomization of patients to PCT guidance or guideline enforced antibiotic therapy is based on a pre-specified computer generated randomization list and concealed by using a centralized password-secured website [21]. This website provides all study-related information including guidelines and patient flow. The randomization is stratified by the participating clinic and the type of LRTI (acute bronchitis, AECOPD, CAP).

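### Centre is a randomisation factor but is left out of the primary confidence interval: a minor, conservative mismatch that is free to correct

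*Protocol article*

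**What the plan says.** The Intervention section states: "The randomization is stratified by the participating clinic and the type of LRTI", the types being acute bronchitis, AECOPD and CAP. The abstract (Methods and design) agrees: allocation "is stratified by centre and type of lower respiratory tract infections". With six hospitals and three types this makes 18 randomisation strata.

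The section on sample size and statistical considerations defines the decisive analysis as "A (two-sided) 90% confidence interval for the difference of the disease-specific failure rates", which "will be calculated based on Cochran's test stratified by type of LRTI". Non-inferiority is concluded if that interval excludes 7.5 percentage points or more. The same section brings in centre, with physician, as a random effect, but only in a second-step logistic regression that explores prognostic factors. No reason is given for keeping one randomisation factor in the primary interval and dropping the other.

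**The concern.** Stratified allocation tends to balance the arms within each centre, so differences between centres largely cancel from the treatment comparison. An analysis that ignores centre still counts those differences in its standard error. To the extent that centres differ, the estimated standard error is larger than the true one, the interval is wider than necessary and the test is conservative. The cost would be some lost precision and power in the one comparison that decides the trial. A second cost is an avoidable choice between two defensible intervals if the upper limit falls close to 7.5 points.

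This is not a detail that an article leaves to the full analysis plan, because the article names the strata of the primary interval.

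**Working it through.** **1. The plan's own figure.** The inputs come from the sample size section: 20% failure in both arms ("if losses to follow-up are treated as failures, the failure rate of all patients may increase to 20"%), a margin of 7.5 points, one-sided 5%, power 90%.

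- Unpooled normal approximation: n per arm = (1.645 + 1.282)² × 2 × 0.20 × 0.80 / 0.075² ≈ 488, or 976 in total.
- Farrington-Manning restricted variance: 982 in total.
- The stated 1002 is within 3% of both.
- At 501 per arm: SE = √(2 × 0.16 / 501) = 0.02527, and power = Φ(0.075/0.02527 − 1.645) = 90.7%. This takes no credit for stratification.

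**2. Analytic check.** Between-centre failure rates are not in the article, so I assume ranges around 20%, with six equal centres, evenly spaced rates and allocation balanced within centres. Let t = 0.16 be the total variance and w the mean of p(1 − p) over centres.

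- Half-width: 1.645 × √(2t/501) ignoring centre, 1.645 × √(2w/501) with centre.
- Power: Φ((0.075 − half-width) / √(2w/501)).
- One-sided error ignoring centre: 1 − Φ(1.645 × √(t/w)).

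Example for centre rates of 10% to 30%: w = 0.16 − 0.00467 = 0.15533, and √(w/t) = 0.985, so the interval is 1.5% narrower.

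| Assumed centre rates | Half-width ignoring / with centre (points) | Narrower by | Power ignoring / with centre | One-sided error ignoring centre |
|---|---|---|---|---|
| all 20% | 4.157 / 4.157 | 0% | 90.7 / 90.7% | 5.00% |
| 17-23% | 4.157 / 4.152 | 0.13% | 90.7 / 90.8% | 4.98% |
| 15-25% | 4.157 / 4.142 | 0.37% | 90.8 / 90.9% | 4.94% |
| 10-30% | 4.157 / 4.096 | 1.5% | 91.0 / 91.4% | 4.75% |
| 5-35% | 4.157 / 4.018 | 3.3% | 91.4 / 92.3% | 4.44% |

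**3. Simulation of 3 against 18 strata.** This used the Mantel-Haenszel risk difference with the Sato variance, 1002 patients and 20,000 trials per scenario. Assumed: centre sizes in proportion to the beds in Table 1, an LRTI mix of 10/20/70%, and type-specific rates of 10/20/21.5%.

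| Centre spread | Narrower with 18 strata | Power, 3 / 18 strata | One-sided error, 3 / 18 strata |
|---|---|---|---|
| none | 0.0% | 91.0 / 91.0% | 5.0 / 5.0% |
| ±3 points | 0.1% | 91.2 / 91.2% | 5.0 / 5.1% |
| ±5 points | 0.3% | 90.4 / 90.5% | 4.8 / 4.9% |
| ±10 points | 1.3% | 91.3 / 91.6% | 4.7 / 4.9% |

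The Monte Carlo error of the one-sided error is √(0.05 × 0.95 / 20,000) ≈ 0.15 points, so values of 5.0% and 5.1% cannot be told from 5%. Using 18 unequal cells causes no visible loss.

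**4. Normal centre effects on the logit scale.** 4,000 trials per setting, 1002 patients, about 20% failure.

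| Assumed SD | SE, type only | SE, centre × type | SE reduction | Power, type only / centre × type |
|---|---|---|---|---|
| 0.3 | 0.02570 | 0.02554 | 0.6% | 89.7 / 89.7% |
| 0.5 | 0.02589 | 0.02544 | 1.7% | 90.6 / 91.2% |
| 0.8 | 0.02635 | 0.02521 | 4.3% | 89.0 / 90.2% |

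A further simulation with bed-proportional centres and an unequal LRTI mix gave SE reductions of about 0.6%, 1.6% and 4.1%, power gains of about 0 to 1.4 points, and a one-sided error of about 4.3% to 5% for the type-only interval.

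**The case against.** The strongest reply is that the harm is unproven and small. Whether the interval is wider at all depends on centre differences that the article does not report. Bed numbers from 252 to 694 show that the hospitals differ in size, not in failure risk. The Setting section calls their length of stay comparable, and all six are public hospitals working under one web-enforced protocol. At centre rates of 10% to 30% the half-width changes by 4.157 − 4.096 = 0.06 points against a 7.5-point margin. The SD of 0.8 is extreme: one SD either side of 20% already runs from about 10% to 36%. LRTI type is already in the primary analysis, and centre effects are examined in a later model.

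Most of this stands, and it sets the size of the point. It does not remove the mismatch, because the exploratory model does not yield the interval that is compared with 7.5 points. Centre differences are also not far-fetched. The sites include secondary and tertiary clinics, the composite includes ICU admission and readmission, and losses to follow-up count as failures; each of these can vary by site.

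A reader might infer that the primary interval is definitely too wide, or that its 5% error rate cannot be trusted. The documents support neither. The excess width is conditional on unreported centre differences, and the departure from 5% is on the safe side.

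**Conclusion.** The mismatch between the randomisation strata and the primary analysis strata is certain; its effect is minor and conservative. With no centre differences there is none. With assumed logit SDs of 0.3, 0.5 and 0.8, the standard error is about 0.6%, 1.6% to 1.7% and 4% smaller when centre is included, and power rises by 0 to about 1.4 points. The one-sided error of the planned interval is at or below 5%, so a finding of non-inferiority would stay valid.

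It might also be inferred that the trial has the wrong size, since the SD 0.8 row equates to 1002 × (1 − (0.02521/0.02635)²) ≈ 85 patients. That does not follow: 1002 is a minimum derived without credit for stratification, and it gives about 90% power either way.

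These figures rest on assumed centre spreads, an assumed LRTI mix and type-specific rates, and allocation that balances the arms within strata. If balance within centres were poorer, the type-only interval would be closer to its nominal error.

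**What to change.** State that the primary 90% confidence interval for the risk difference uses Cochran/Mantel-Haenszel weights over the centre-by-LRTI-type randomisation strata: 18 cells of unequal size, which these weights tolerate. Use the stratum recorded at randomisation. This matters for acute bronchitis, where the Intervention section plans a later chest X-ray that may revise the diagnosis. Keep the type-only interval as a pre-specified sensitivity analysis.

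The cost is a change of wording. Centre is already recorded, and no extra patients, data or change in patient care are needed. The article describes the trial as ongoing, so the change should be fixed before outcomes are seen by arm.

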## Background

Lower respiratory tract infections (LRTI) including acute bronchitis, acute exacerbations of chronic obstructive pulmonary disease (AECOPD) and community-acquired pneumonia (CAP), account for almost 10% of the worldwide burden of morbidity and mortality, and thus, importantly contribute to antibiotic overuse and allocation of health resources [1,2]. Although most LRTI are of viral origin, approximately 75% of antibiotics are prescribed because viral etiology and disease severity are difficult to recognize with traditional clinical and laboratory means [2]. Current criteria for assessing the severity of CAP, such as the pneumonia severity index (PSI) and the CAP severity on presentation to hospital scale (CURB65) are well validated, but have important drawbacks for routine care [3-6]. They only predict mortality in CAP and depend mainly on age, thereby underestimating the disease-related morbidity in younger patients. Furthermore, they dichotomize continuously measured values (e.g. respiratory rate) into normal and abnormal values and show a high intra-observer variation of around 10 percent.

A widely used approach to estimate the probability of a bacterial origin and the disease severity of a LRTI is the use of the C-reactive protein. However, this biomarker lacks sensitivity and specificity, and thorough studies about its effect on antibiotic use are lacking [7,8]. More promising appears to be the level of circulating procalcitonin (PCT) which has been demonstrated to correlate with the likelihood for a bacterial infection [7,9]. We conceived and successfully validated PCT guided diagnosis using cut-off ranges in the continuum of LRTI in four intervention trials by randomizing patients to PCT guided antibiotic prescription versus standard care and monitored clinical outcome. In these trials we circumvented the gold standard dilemma for the etiologic diagnosis of LRTIs by assuming absence of serious bacterial infection in patients recovering without antibiotics [10-14].

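### The primary non-inferiority interval adjusts for LRTI type only; a pre-specified adjustment for baseline age and severity would make it modestly narrower at little cost

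*Protocol article*

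**What the plan says.** All references are to the Protocol article.

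- **Primary analysis** (Sample size and statistical considerations). A two-sided 90% confidence interval for the difference in 30-day failure rates "will be calculated based on Cochran's test stratified by type of LRTI". Non-inferiority means a failure rate on procalcitonin guidance that is "less than 7.5% higher compared to those on guidelines-enforced management". Losses to follow-up count as failures in both arms.
- **Use of other baseline factors** (same section). In a second, exploratory step the primary endpoint is related to potential prognostic factors by logistic regression: "The factors that will be considered are: age, sex, LRTI subgroup, PSI and CURB65 score in CAP patients", with GOLD criteria and Anthonisen type for COPD patients. Centre is examined there as a random effect.
- **What is said about the scores** (Background). PSI and CURB65 "are well validated, but have important drawbacks for routine care". The same paragraph limits them to predicting mortality in CAP and says that they depend mainly on age.
- **Randomisation** (Intervention). Stratified by clinic and by type of LRTI.

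**The concern.** Within one type of LRTI, patients of different age and severity are likely to differ in their risk of failure. A comparison stratified by type alone leaves that variation in the standard error. Severity is also not a randomisation stratum, so its balance between arms is left to chance. One confidence bound set against 7.5 points decides the trial, so any avoidable width lowers the chance of showing non-inferiority when it is true. The baseline measures are needed anyway for the exploratory model, so using them in the primary estimate would take no new data. The question is how much would be gained.

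**Working it through.** **1. Inputs from the article.** Margin 7.5 points. Error rate and power: "with a one-sided type I error of 5% and a power of 80% to 90" per cent. Planning rates: "the risk of disease-specific failure in evaluable patients is assumed to be around 15" per cent and, with losses counted as failures, "the failure rate of all patients may increase to 20" per cent. Size: "a minimal number of 1002 patients (501 patients per arm) are required". In Table 2, 1002 is the 90% power entry for 20% failure and a 7.5-point margin.

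**2. The plan's own figure.** With the unpooled formula, n per arm = (1.645 + 1.282)² × 2 × 0.20 × 0.80 / 0.075² = 487.2, rounded up to 488, or 976 in total. The Farrington-Manning formula gives 982 and a continuity-corrected one 1030. The stated 1002 lies among these and is reproduced within 3%.

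**3. Precision without covariates, 501 per arm, 20% failure.** SE = √(2 × 0.16 / 501) = 0.02527. The 90% half-width is 1.645 × 0.02527 = 4.16 points. Power = Φ(0.075 / 0.02527 − 1.645) = 90.7%.

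**4. Implied losses.** If 15% becomes 20% because losses are added as failures, 0.15 + 0.85 × L = 0.20, so L = 0.05 / 0.85 = 5.9%. Losses are then 5.9 / 20, or about 29%, of counted failures. If they are unrelated to severity, they dilute its prognostic value.

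**5. Effect of adjustment.** If the covariates explain a share R² of the outcome variance within type, the standard error is multiplied by about √(1 − R²). The article gives no R² or AUC, so a range is assumed. The simulation used 1002 patients, 1500 trials per scenario and a true difference of zero. One baseline severity variable stood for all the covariates, and 5.9% of patients were lost at random and counted as failures. The mix of LRTI types and their differences in risk also had to be assumed. The comparison is between a Cochran (Mantel-Haenszel-weighted) risk difference by type and a logistic-standardised risk difference that adds the severity variable.

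| Assumed AUC | R² within type | 1 − √(1 − R²) | Simulated half-width, Cochran → adjusted (points) | Narrower by | Power |
|---|---|---|---|---|---|
| 0.62 | 0.015 | 0.8% | 4.14 → 4.12 | 0.5% | 89.3% → 89.7% |
| 0.69 | 0.043 | 2.2% | 4.14 → 4.06 | 2.0% | 90.7% → 91.9% |
| 0.75 | 0.083 | 4.2% | 4.14 → 3.98 | 3.9% | 92.0% → 93.5% |

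Simulation error on power is about 0.7 points, which is why the unadjusted column varies. The formula and the simulation agree closely.

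**6. In patients.** The extra patients that would give the same precision are 1002 × [1 / (1 − w)² − 1], where w is the narrowing. For w = 0.005, 0.020 and 0.039 this is about 10, 41 and 83.

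**7. With no losses (15% failure).** The narrowing is 0.9%, 3.0% and 5.9%.

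**The case against.** The strongest reply is that nothing here is wrong. A Cochran interval stratified by LRTI type is valid, uses a randomisation stratum, is on the scale of the margin and has about 90% power. The 1002 is also a minimum. All of this stands.

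The case for strong prognostic value is limited too. The factors are called only potential. PSI and CURB65 are tied to mortality in CAP, while the endpoint also counts recurrence, complications, ICU admission and readmission. No severity score is listed for acute bronchitis. This also stands, and it is why the gain is put at a few per cent.

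Three stronger readings are tempting, and the article does not support them:

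- **That chance imbalance in severity biases the result.** For an assumed R² of 2%, 5% or 10%, imbalance would move the observed difference with SD √R² × 2.53 points, a 95% range of about ±0.7, ±1.1 or ±1.6 points. The planned interval already allows for this at its nominal error rate. Adjustment removes variance, not bias.
- **That no severity-adjusted treatment comparison is planned, because the logistic model has no treatment term.** The article does not say whether arm is included. A supplementary adjusted analysis may stand in an analysis plan that is not shown.
- **That the gain is about twice as large.** Starting from the unstratified 4.16 points and ignoring losses, an AUC of about 0.70 would give 3.96 points, or 4.7% narrower. That credits adjustment with what stratification by type already delivers and leaves out the dilution by losses. With both allowed for, the figure is about 2%.

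A practical objection also has weight: the trial is ongoing and the intervention is open, so changing the primary estimator is more than an edit of wording. It calls for a documented change made before anyone has compared outcomes by arm.

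**Conclusion.** The point holds as an efficiency improvement. The stated primary interval is adjusted for LRTI type only, and baseline measures that the trial itself regards as possibly prognostic are kept for a later exploratory model. Using them would narrow the 90% interval by about 0.5% to 4% with losses counted as failures, and by up to about 6% without losses. Power would rise by about 0.4 to 1.5 points.

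The facts and the direction are firm, provided that the factors are prognostic at all. The size rests on assumptions: an AUC of 0.62 to 0.75, losses unrelated to severity, an assumed mix of LRTI types, and one severity variable standing for several. It should not be read as saying that the planned analysis is invalid or the trial underpowered.

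**What to change.** Before any outcome comparison by arm, pre-specify the primary 90% interval as a standardised (marginal) risk difference from a logistic model, with a delta-method or bootstrap interval:

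- **Terms:** arm, LRTI type, age, and baseline severity nested within type (PSI class in CAP; GOLD stage and Anthonisen type in AECOPD). Do not enter PSI and CURB65 together.
- **Centre:** preferably include it, as the other randomisation stratum.
- **Missing baseline values:** state a rule, such as a missing category for GOLD stage, which depends on post-bronchodilator spirometry (Participants).
- **Scale:** compare the marginal risk difference with the same 7.5-point margin. A conditional odds ratio cannot be compared with it.
- **Sensitivity analysis:** keep the Cochran interval stratified by LRTI type.

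The cost is a short, dated change to the analysis text, with no new patients or measurements. The downside is that the primary result becomes model-assisted, so covariates, coding and interval method must all be fixed in advance.
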